## Abstract

(1) Background: Heart failure (HF) with preserved ejection fraction (HFpEF) accounts for approximately 50% of all patients with HF. In the absence of pharmacological treatments that have been successful in reducing mortality or morbidity in this pathology, physical exercise is recognized as an important adjunct in the treatment of HF. Therefore, the objective of this study is to compare the efficacy of combined training and high intensity interval training (HIIT) on exercise capacity, diastolic function, endothelial function, and arterial stiffness in participants with HFpEF. (2) Methods: The ExIC-FEp study will be a single-blind, 3-arm, randomized clinical trial (RCT) conducted at the Health and Social Research Center of the University of Castilla-La Mancha. Participants with HFpEF will be randomly assigned (1:1:1) to the combined exercise, HIIT or control group to evaluate the efficacy of physical exercise programs on exercise capacity, diastolic function, endothelial function, and arterial stiffness. All participants will be examined at baseline, at three months and at six months. (3) Results: The findings of this study will be published in a peer-reviewed journal. (4) Conclusions: This RCT will represent a significant advance in the available scientific evidence on the efficacy of physical exercise in the treatment of HFpEF.

## 1. Introduction

Heart failure (HF) is a chronic disease with a major and increasingly serious social and health impact. It currently affects more than 23 million people worldwide, and its prevalence is expected to increase by approximately 25% by 2030 [1]. Two distinct phenotypes of HF have been identified: HF with reduced ejection fraction (HFrEF) and HF with preserved ejection fraction (HFpEF) [2]. In the last decade, HFpEF has accounted for approximately 50% of all patients with HF. In general, the prognosis of HFpEF is slightly better than the prognosis of HFrEF [3,4]. The increasing prevalence of HFpEF is attributed to increased life expectancy, better awareness of the diagnosis [5] and increased prevalence of major underlying risk factors (e.g., obesity, diabetes mellitus and hypertension) [6].

Insufficient physical activity, poor cardiorespiratory fitness and obesity have been identified as significant risk factors for cardiovascular disease (CVD) in general and HF in particular, mainly in patients with HFpEF [7,8,9,10]. HFpEF is a clinical syndrome in which the heart is unable to supply the amount of oxygen required by the tissues according to their needs or does so only at the cost of excessively increased left ventricular filling pressures, despite the existence of a left ventricular ejection fraction (LVEF) within the normal range. In the absence of pharmacological treatments that have been successful in reducing the mortality or morbidity of this pathology, the therapeutic goal for these patients is based on improving quality of life (QoL) by improving exercise capacity. Physical exercise is recognized as an important adjunct in the treatment of HF and is recommended by the American College of Cardiology/American Heart Association (ACC/AHA) and European Society of Cardiology (ESC) guidelines [11,12]. Currently, aerobic exercise is the most studied physical exercise in this population, but in recent years, the combination of aerobic exercise with strength training (combined exercise (CE)) and high intensity interval training (HIIT) have emerged.

To date, several systematic reviews and meta-analyses of randomized clinical trials (RCTs) have suggested that physical exercise can lead to important changes in different parameters of exercise capacity, such as fitness as measured by VO2max and diastolic function as measured by echocardiographic parameters [13,14,15,16,17,18,19,20,21]. However, most of these systematic reviews and meta-analyses analyzed all types of exercise together and did not explore the effect on endothelial function and arterial stiffness. In addition, there are currently eleven published RCTs [22,23,24,25,26,27,28,29,30,31,32] on the effect of physical exercise on different parameters of exercise capacity, mainly VO2max. Most of these compare the effect of moderate aerobic exercise versus a control group, while two clinical trials and one pilot study compare moderate aerobic exercise versus HIIT (with one of these studies including a control group) and a single pilot study comparing CE versus a control group. Only two studies analyzed the effect of moderate aerobic exercise on endothelial function and arterial stiffness [28,29]. Recently, a network meta-analysis compared the effect of aerobic exercise, CE and HIIT, supporting the well-known effect of aerobic exercise but showing promising findings for CE and HIIT not only on VO2max but also on diastolic function [33].

Due to the lack of studies analyzing the effect of CE and HIIT and their impact, not only on improving exercise capacity and cardiac function but also on endothelial function and arterial stiffness, in participants with HFpEF, this RCT will be conducted to (1) compare the efficacy of CE and HIIT on exercise capacity, diastolic function, endothelial function and arterial stiffness in patients with HFpEF and (2) to compare the efficacy of CE and HIIT on QoL in participants with HFpEF.

## 2. Materials and Methods

### 2.1. Design

The ExIC-FEp study will be a single-blind, three-arm RCT to analyze two types of supervised physical exercise in participants with HFpEF for 6 months. Additionally, this protocol for RCT has been registered for clinical trials (NCT05726474).

### 2.2. Setting

The recruitment of participants with HFpEF will be carried out in the Cuenca I, II and III primary health centers and the cardiology and internal medicine services of the Hospital Virgen de la Luz of the Castilla-La Mancha Health Service (SESCAM). The professionals of these services will be informed of the RCT and its purpose to recruit patients with HFpEF, who will then be invited via these healthcare professionals, as well as information meetings and posters, to participate in the RCT.

### 2.3. Participants 

The study will include sedentary participants with stable symptomatic HFpEF, diagnosed according to ESC criteria [34]. Participants with HFrEF will be excluded, as well as patients with other causes of HF symptoms, such as significant valvular or coronary heart disease or uncontrolled hypertension or arrhythmias. The inclusion and exclusion criteria are shown in Table 1.

For inclusion and exclusion criteria, a complete echocardiographic examination incorporating all two-dimensional and Doppler data will be performed. In addition, the patient’s clinical assessment, exercise capacity and medical history will be taken into account and spirometry will be performed to rule out significant pulmonary disease.

### 2.4. Randomization

After informed consent and screening, participants will be randomly distributed (1:1:1) using EPIDAT 4.2 software (Figure 1) into three groups: group 1, CE (continuous aerobic exercise with moderate intensity strength exercises); group 2, HIIT; and group 3, control group (CG).

### 2.5. Intervention

#### 2.5.1. Training Interventions

Participants in groups 1 and 2 will perform supervised intensity training on an ergometer bicycle. Exercise intensity (relative to maximum heart rate (HRmax) and maximum heart rate percentage (%HRmax) will be determined by a maximal cardiopulmonary stress test at baseline. 

**CE** (Group 1). Participants will exercise for 40 min three times a week on an ergometer bike at 50–60% of VO2max, 60–70% of HRmax and 11–13 on the Borg scale, without respiratory distress. In addition, strength training (bench press, leg press, leg curl, rowing machine, triceps dip, pec pull) will be performed twice a week. The strength training will be performed with 15 repetitions per exercise per session, with a workload corresponding to 60% to 65% of the 1 repetition maximum (1RM) measured at the beginning and end of the intervention.

**HIIT** (Group 2). Participants will perform three training sessions per week. Each training session will begin with a 10-min warm-up at moderate intensity (corresponding to 50–60% of VO2max, 60–70% of HRmax, and 11–13 on the Borg scale, without respiratory distress) before four 4-min intervals at high intensity (corresponding to 85–90% of VO2max, 90–95% of HRmax, and 15–17 on the Borg scale, with mild respiratory distress). Each interval will be separated by 3 min of active pauses, with an HRmax of 50–70%. The training session will end with 3 min of cool down at moderate intensity (corresponding to 50–60% of VO2max, 60–70% of HRmax, and 11–13 on the Borg scale, without respiratory distress). The total exercise time will be 40 min for the HIIT group. 

#### 2.5.2. Control Group (Group 3)

CG participants will receive standard advice on the general cardiovascular benefits of physical exercise according to current guidelines (30 min of walking on most days of the week) [35] and will continue their usual daily leisure-time physical activity throughout the study.

#### 2.5.3. Duration of the Intervention

Interventions will last 3 months. Figure 2 shows the flow chart for participant inclusion and follow-up: screening, inclusion and exclusion, randomization, baseline testing, and testing after follow-up. 

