### 2.9. Sample Size Calculation

The sample size calculation is based on data from the RCT by Mueller et al. [31] which reveals that 21 participants per group would provide 80% power at *p* < 0.05 to detect a statistically significant result for VO2max, the primary outcome. Considering the three groups (CE, HIIT and GC) and a dropout rate of 20%, a total of 72 participants will be recruited.

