### 2.10. Statistical Analysis

The statistical analysis will consist of three phases. The first will consist of testing the effectiveness of randomization in creating three comparable groups of participants with HFpEF, exploring the presence of outliers, and testing the degree of adjustment of the main variables to the normal distribution.

In the second phase, ANCOVA models will be used (baseline and 3 months) in which the dependent variables will be each outcome variable, and the intervention will be the fixed effect (2 = CE, 1 = HIIT and 0 = GC), adjusted for baseline, age, sex and socioeconomic status. The results will be expressed as absolute differences in changes in variables between baseline and final measurements (95% confidence interval (95% CI)). Bonferroni post hoc tests will be performed for paired comparisons.

In the third phase, a comparison of CE, HIIT and CG will be performed using the propensity score matching method to take into account covariate imbalance in baseline measurements between subjects. The propensity score estimates the effect of the intervention using a causal inference model, which explains what would have happened if all subjects in the intervention and control groups had the same characteristics at baseline. Each subject is matched to a subject with similar characteristics using a 0.40 caliper using the psmatch2 command.

All analyses will be performed by INTENT TO TREAT, keeping subjects in the originally assigned intervention or control group, regardless of the number of physical activity program sessions attended, and considering the CONSORT.

The results with *p* < 0.05 will be considered statistically significant. The analysis will be performed with the STATA16 statistical package. 

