**Figure 2 jcm-12-03535-f002:**
[figure not shown]
Flow chart for participant inclusion and follow-up: screening, inclusion and exclusion, randomization, baseline testing, and testing after follow-up.

**Table 1 jcm-12-03535-t001:** Inclusion and exclusion criteria.

Inclusion Criteria	Exclusion Criteria
1. HFpEF (diagnosis according to ESC 2021 criteria): a. Signs and symptoms of HF. b. LVEF ≥ 50%. c. Objective evidence of cardiac structural and/or functional abnormalities consistent with the presence of left ventricular diastolic dysfunction/elevated left ventricular filling pressures, including elevated natriuretic peptide. 2. Sedentary men and women (structured exercise < 2 × 30 min/week). 3. Age ≥ 40 years. 4. Written informed consent. 5. Clinically stable for ≥6 weeks. 6. Optimal medical treatment for ≥6 weeks.	1. Noncardiac causes of HF symptoms: -Significant valvular or coronary artery disease. -Uncontrolled hypertension or arrhythmias. -Primary cardiomyopathies. 2. Significant pulmonary disease (FEV1 < 50% predicted, GOLD III-IV). 3. Exercise disability or conditions that may interfere with exercise intervention. 4. Myocardial infarction within the last 3 months. 5. Signs of ischemia during maximal cardiopulmonary stress test. 6. Comorbidity (renal failure, cancer, cognitive impariment) that may influence prognosis at 1 year. 7. Participation in another clinical trial.

ESC, European Society of Cardiology; HF, heart failure; HFpEF, heart failure with preserved ejection fraction; LVEF, left ventricular ejection fraction; GOLD, Global Initiative for Chronic Obstructive Lung Disease; FEV1, forced expiratory volume in the first second.

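### Baseline testing is listed after randomisation, so effort-dependent and self-reported baselines may be measured with the allocation known, and the timing of the maximal test needed for exclusion criterion 5 is not reconciled.

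*Protocol article*

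**What the plan says.** - **Order of steps.** Section 2.5.3 describes the flow as "screening, inclusion and exclusion, randomization, baseline testing, and testing after follow-up". The Figure 2 caption uses the same sequence.
- **Randomisation.** Section 2.4: "After informed consent and screening, participants will be randomly distributed (1:1:1) using EPIDAT 4.2 software". Baseline testing is not named as a prior step.
- **Eligibility.** Table 1, exclusion criterion 5, is "Signs of ischemia during maximal cardiopulmonary stress test". Section 2.3 says that for eligibility "the patient’s clinical assessment, exercise capacity and medical history will be taken into account".
- **Maximal test.** Section 2.5.1 says that exercise intensity "will be determined by a maximal cardiopulmonary stress test at baseline".
- **Use of the baseline.** Section 2.9 sizes the trial "to detect a statistically significant result for VO2max, the primary outcome". Section 2.10 fits ANCOVA models "adjusted for baseline, age, sex and socioeconomic status", reports differences in change from baseline, and adds a propensity-score phase to deal with baseline imbalance.
- **Blinding.** Section 2.1 calls the trial single-blind and does not say who is blinded.

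**The concern.** A baseline covariate is safe to adjust for because allocation cannot have influenced it. That protection is lost if the measurement is taken once the participant knows the arm. VO2max, workload and walk distance depend on effort, and SF-12 and MLWHFQ are self-reported. Someone told that they will receive advice only, or that they will be trained, may perform or answer differently.

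Such a shift would enter the ANCOVA and the change from baseline. It could also pass for chance imbalance, both in the first analysis phase, which checks whether randomisation produced comparable groups, and in the propensity-score phase, which would then match on it.

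There is a second issue. One eligibility criterion can be judged only from a maximal cardiopulmonary test. The article ties the pre-training maximal test to baseline and lists baseline testing after randomisation, yet it also lists inclusion and exclusion before randomisation.

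**Working it through.** The point concerns the order of procedures. The plan states no figure to reproduce, so the check sets the statements side by side.

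**Step 1. Where baseline testing falls.** Section 2.5.3 and the Figure 2 caption both give: screening, then inclusion and exclusion, then randomisation, then baseline testing, then follow-up testing. Section 2.4 is consistent with this. No section says that baseline outcomes are measured before allocation.

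**Step 2. Who could know the arm at baseline.** Groups 1 and 2 receive supervised bicycle training (section 2.5.1) and group 3 receives advice (section 2.5.2). Participants cannot be blind to that contrast once told. Blinding an assessor, if that is what single-blind means here, would not change what participants know.

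**Step 3. How a baseline shift reaches the result.** For two arms, the ANCOVA contrast is

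adjusted effect = (difference in follow-up means) − b × (difference in baseline means),

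where b is the within-group slope of follow-up on baseline. If knowing the allocation moves the baseline mean of one arm by s and leaves the follow-up unchanged, the adjusted effect moves by −b × s. With baseline as a covariate, the contrast is the same whether the dependent variable is the final value or the change. An unadjusted change would carry the whole of s.

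The documents give neither b nor s. As an illustration only, assume b from 0.5 to 0.9 and s from 0.1 to 0.3 SD in one arm:

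- smallest: 0.5 × 0.1 = 0.05 SD
- middle slope: 0.7 × 0.1 = 0.07 SD to 0.7 × 0.3 = 0.21 SD
- largest: 0.9 × 0.3 = 0.27 SD

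The sign is open. More effort at baseline in a training arm would understate its benefit, and holding back would overstate it. These values are not expressed as a share of a planned effect, because section 2.9 states no effect size or standard deviation.

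**Step 4. When the maximal test for criterion 5 is done.** There are two readings.

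- *One maximal test.* Section 2.5.1 places it at baseline, and section 2.5.3 places baseline testing after randomisation. Criterion 5 in Table 1 would then have to be applied before randomisation using a test done after it. The three places conflict.
- *Two maximal tests, one at screening and one at baseline.* Criterion 5 can be applied in time, and section 2.3 fits this because exercise capacity is part of the eligibility assessment. The article does not describe a second test, however, and the baseline outcomes are still listed after allocation.

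A third arrangement, in which a single screening test also supplies the baseline value, would remove the problem for VO2max. The listed order would then be wrong as written for that test.

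**The case against.** The strongest reply has four parts.

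1. *The same sequence puts inclusion and exclusion before randomisation.* This is correct. A reader might infer that participants will be excluded after allocation and that the intention-to-treat population is therefore broken. The documents do not support that. Section 2.3 uses exercise capacity for eligibility, no section describes removing anyone after allocation, and section 2.10 keeps participants in their assigned group. What remains is conditional: if there is one maximal test, the statements conflict.

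2. *Being randomised is not the same as being told.* Section 2.4 does not say when the allocation is revealed, and a condensed article may leave that to the full protocol. This is why the point says that the allocation may be known, not that it is. It does not remove the point, because the article states an order, and that order creates the exposure unless disclosure is delayed.

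3. *The evidence is one phrase.* Section 2.5.3 and the caption share the same wording, so they are not independent, and the figure itself could not be examined. The phrase still reads chronologically, and section 2.4 does not contradict it.

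4. *Not every outcome is exposed alike.* Echocardiography, carotid intima-media thickness and pulse wave velocity do not depend on effort or self-report in the way that VO2max, walk distance and quality of life do. This stands and limits the scope. VO2max, for which the trial is sized, is among those exposed.

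**Conclusion.** The point holds in a limited form. As written, baseline outcomes are collected after randomisation in a trial whose participants cannot be blind to the training-versus-advice contrast. Baseline VO2max, walk distance and quality of life may therefore be measured with the arm known, and the primary analysis adjusts for them. The possible bias cannot be quantified from the documents in size or direction. The 0.05 to 0.27 SD range above only shows how the mechanism scales under assumed slopes and shifts, and is not an estimate for this trial.

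The timing of the maximal test behind exclusion criterion 5 is unresolved. Sections 2.5.1 and 2.5.3 and Table 1 conflict if there is only one such test, and must be reconciled.

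This is an improvement that should be made before enrolment, since a baseline measured after allocation cannot be repaired later. The conclusion assumes that the listed order is the intended chronological order and that participants are told their arm at or soon after randomisation.

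**What to change.** Amend sections 2.4 and 2.5.3 and Figure 2 so that all baseline outcome measurements, including the maximal cardiopulmonary test, and all eligibility checks are completed before the allocation is generated and revealed. State in section 2.3 or 2.5.1 whether the maximal test used for criterion 5 is the same test that supplies baseline VO2max and the training intensities. If baseline testing already precedes allocation in practice, correcting the text is enough.

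The cost is a re-ordering of existing visits. The downside is that a few people will complete baseline testing and then not be randomised.

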### 2.6. Criteria for Nonadherence and Prolongation of Training 

For participants to be considered compliant with training, they must attend at least 70% of the possible training sessions within the allotted time. Training compliance will be monitored and documented regularly throughout the trial. If, due to unforeseen circumstances, a participant does not comply with training during the supervised intervention (6 months), supervised training may be extended for up to 4 weeks.

### 2.7. Outcomes

#### 2.7.1. Primary Outcomes

*Exercise capacity by maximal cardiopulmonary exercise test with Ergoline600 ergometer bicycle:*
−Gas analyzer (K5 COSMED): VO2max, ventilation slope/carbon dioxide production (VE/VCO2) per minute, and ventilatory threshold (VT).−Workload measured in watts.−Average exercise time in minutes.−HRmax by Polar H10 heart rate monitor.−A 6-min walking test, in a 30-m corridor, to be performed by walking from one side to the other along this stretch of corridor, which will be delimited by cone-type indicators. These signs will be placed 29 m from each other, leaving 0.5 m at each end for the subject to turn. The test will be performed accompanied by the examiner. The primary test outcome is the final distance walked.

*Echocardiography:*
−Using Sonosite SII Doppler ultrasound (Sonosite Inc., Bothell, WA, USA), the following will be measured: E velocity (m/s), A velocity (m/s), E/A ratio, e’ velocity (m/s), E/e’ ratio, ejection fraction percentage, left ventricular volume index, end-diastolic volume, left ventricular mass, left atrial diameter, isovolume relaxation time, deceleration time (m/s) and left atrial volume index.

*Endothelial function:*
−Carotid intima-media thickness (cIMT): by ultrasound with the Sonosite SII device (Sonosite Inc., Bothell, WA, USA).

*Arterial stiffness:*
−Pulse wave velocity (PWv) and central augmentation index (cAIx) using the Mobil-O-Graph PWA (I.E.M. GmbH, Stolberg, Germany).

*Quality of life:*
−Validated 12-item health questionnaire (SF-12).−Validated Minnesota Living with Heart Failure Questionnaire (MLWHFQ).

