## 4. Discussion

The primary objective of this study will be to compare the effectiveness of CE and HIIT on exercise capacity, diastolic function, endothelial function, and arterial stiffness in participants with HFpEF, and the secondary objective of this study will be to compare the effectiveness CE and HIIT on QoL in participants with HFpEF.

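### Section 2.7.1 lists 25 variables as primary outcomes, while section 2.9 names VO2max as the single primary outcome and the Discussion makes quality of life secondary

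*Protocol article*

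**What the plan says.** Four places in the protocol article bear on which outcome is primary.

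- **Outcome list.** All efficacy variables stand under "2.7.1. Primary Outcomes": cardiopulmonary exercise variables and the 6-minute walk, echocardiography, carotid intima-media thickness, two arterial stiffness indices, and two quality-of-life questionnaires (SF-12 and MLWHFQ). The next heading, 2.7.2, is for covariables. Section 2.7 has no secondary-outcome heading.
- **Sample size (section 2.9).** The 21 participants per group are said to give 80% power "to detect a statistically significant result for VO2max, the primary outcome". One variable is named, in the singular.
- **Objectives.** The Introduction (objective 1) and the Discussion (primary objective) cover exercise capacity, diastolic function, endothelial function and arterial stiffness. Quality of life is separate: "the secondary objective of this study will be to compare the effectiveness CE and HIIT on QoL in participants with HFpEF".
- **Analysis (section 2.10).** ANCOVA models are fitted at baseline and 3 months, "in which the dependent variables will be each outcome variable". Bonferroni is applied post hoc to the paired comparisons between arms. One threshold, p < 0.05, applies to all results.

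**The concern.** A trial has to say before the data are seen which result decides it. Here a reader can take the answer from section 2.9 (one variable), from the Discussion (four domains, quality of life secondary) or from section 2.7.1 (everything measured for efficacy). These cannot all hold.

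The stake is how the trial is reported. If VO2max showed nothing but deceleration time or HRmax crossed p < 0.05, section 2.7.1 would allow that to be presented as a positive primary outcome, although the stated 80% power refers to VO2max alone. The Bonferroni step gives no protection here, because it works across the three pairs of arms within one outcome and not across outcomes.

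**Working it through.** **Step 1. Count the variables in section 2.7.1.**

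| Domain | Variables | Count |
|---|---|---|
| Exercise capacity | VO2max, VE/VCO2, VT, workload, exercise time, HRmax, 6-minute walk distance | 7 |
| Echocardiography | E, A, E/A, e’, E/e’, ejection fraction, LV volume index, end-diastolic volume, LV mass, LA diameter, isovolume relaxation time, deceleration time, LA volume index | 13 |
| Endothelial function | cIMT | 1 |
| Arterial stiffness | PWv, cAIx | 2 |
| Quality of life | SF-12, MLWHFQ | 2 |
| **Total** | 7 + 13 + 1 + 2 + 2 | **25** |

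Each questionnaire is counted as one variable. If SF-12 were scored as two summary scores, which the article does not say, the total would be 26.

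**Step 2. Set the count beside the other sections.** Section 2.9 has 1 primary outcome. The domains of the primary objective in the Discussion cover 25 − 2 = 23 of the listed variables, and the two questionnaires conflict with it directly.

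**Step 3. False-positive chance if any one significant variable counted as success.** The plan gives no figure of its own to reproduce. Assumptions: no true effect on any variable, and one three-arm test per variable at 0.05.

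- Independent outcomes: 1 − (1 − 0.05)^25 = 1 − 0.95^25 = 0.723.
- Without the two questionnaires: 1 − 0.95^23 = 0.693.
- Expected number of false positives, whatever the correlation: 25 × 0.05 = 1.25.

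Independence is not realistic. The list "E velocity (m/s), A velocity (m/s), E/A ratio, e’ velocity (m/s), E/e’ ratio, ejection fraction percentage, left ventricular volume index, end-diastolic volume" already contains two ratios (E/A and E/e’) together with their components, and several variables come from the same exercise test. The article gives no correlations, so a common correlation was assumed and varied. The simulation used 25 equicorrelated normal outcomes, 3 × 21 participants and an omnibus F-test for each outcome, with 4,000 runs per row:

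| Assumed common correlation | Chance of at least one p < 0.05 |
|---|---|
| 0 | 0.721 |
| 0.3 | 0.610 |
| 0.5 | 0.488 |
| 0.7 | 0.333 |
| 0.9 | 0.175 |

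A repeat with 20,000 runs per row gave 0.721, 0.613, 0.482, 0.330 and 0.172, so the table is good to about one percentage point.

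**Step 4. Could all 25 stay primary with the error controlled?** Bonferroni across outcomes gives 0.05/25 = 0.002 per outcome. The effect size behind the 21 per group is not stated. A two-sided two-sample t-test with 21 per group, 80% power and alpha 0.05 implies a standardized difference of about 0.89. At alpha 0.002, that difference has about 35% power with 21 per group, and 80% power needs about 42 per group before dropout.

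**The case against.** Four points can be made for the plan.

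- **Multiplicity across outcomes may be set out in an analysis plan that is not shown.** This stands, and the lack of such a rule in a condensed article is not held against the plan. But which outcome is primary is stated in this article, in ways that conflict, and no further document can make sections 2.7.1 and 2.9 agree.
- **The list follows the primary objective.** This is partly right: 23 of the 25 variables belong to the four domains of the primary objective. The two questionnaires do not, and section 2.9 still names one variable.
- **VO2max is plainly the intended primary outcome.** Section 2.9 supports this. If it governs, the primary analysis concerns one outcome, with Bonferroni for the arm pairs, and the inflation in Step 3 does not arise. That is a reason to bring section 2.7.1 into line with it.
- **No success rule is given.** This also stands. A reader might infer that the trial will be declared positive on any one of 25 variables, or that its false-positive rate is 72%. The article says neither. The first is a use that the text permits; the second is the upper end of a conditional range. Nor is the plan without any adjustment, since Bonferroni covers the arm pairs within each outcome.

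**Conclusion.** The contradiction is explicit and should be corrected before results are seen: 25 primary outcomes in section 2.7.1 against one in section 2.9, and quality of life primary in the list but secondary in the Discussion. With every outcome judged at 0.05, the text leaves room to report any significant variable as a primary success.

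The size is conditional. If the list in section 2.7.1 governs, any single significant variable counts as success and nothing truly works, the chance of at least one false positive is about 18% at an assumed common correlation of 0.9, about 48% at 0.5 and 72% under independence. The low end is still more than three times the nominal 5%. If section 2.9 governs, there is no inflation across primary outcomes.

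**What to change.** - In section 2.7.1, keep VO2max at 3 months as the only primary outcome. This matches section 2.9 and the time point of the ANCOVA in section 2.10.
- Move all other listed variables, including both quality-of-life questionnaires, to a new secondary/exploratory section.
- Reword the objectives in the Introduction and the Discussion. Both now place diastolic function, endothelial function and arterial stiffness in the first or primary objective, and would otherwise contradict the corrected list.
- Report the non-primary variables as supportive, with confidence intervals, unless a multiplicity rule across them is pre-specified.

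One dependency: the Abstract has assessments at three and six months, and sections 2.5.3 and 2.6 give different lengths for the intervention (3 and 6 months). Those passages must be reconciled, and the primary time point confirmed against the result.

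The cost is protocol wording, with no extra participants or measurements. The small downside is that the other domains can no longer be headlined as primary. Whether the registry entry also needs changing cannot be judged from the article, which gives only its number.
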